### Participants

The participants will be children aged 7 to 12 years with an anxiety disorder or subclinical anxiety symptoms as well as one of their parents or a legal representative. The following eligibility criteria will be considered:The child is aged 7 to 12 years;The child has a primary diagnosis of an anxiety disorder or clinically significant anxiety symptoms;Both the child and the parent/legal representative are able to speak, read and understand Portuguese;Both the child and the parent/legal representative have internet access;The child does not have a diagnosis of a psychotic disorder, bipolar disorder, intellectual disability or autism spectrum disorder;The child does not have severe current suicidal ideation;The child is on a stable dose of psychotropic medication for at least 1 month prior to the baseline assessment;The child is not currently receiving other types of psychotherapy.

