#### Participant selection

The eligibility criteria for the study will be assessed in an initial interview with parents and children. First, a researcher will briefly explain the goal and procedures of the study and the initial interview and will ask both the parents and the child for consent to administer the Anxiety Disorders Interview Schedule for Children (ADIS-IV-C) [44]. The ADIS-IV-C is a semistructured interview for assessing the presence of anxiety difficulties and diagnosis (e.g., separation anxiety, social phobia, specific phobia, panic disorder, agoraphobia), obsessive–compulsive disorder, posttraumatic stress disorder, depressive disorder, and externalizing disorders (e.g., attention deficit and hyperactivity disorder) in youth aged 6 to 17 years according to the diagnostic criteria of the Diagnostic and Statistical Manual of Mental Disorders (DSM-IV; APA, 1994). Parents and children will be interviewed together by a clinical psychologist, according to the procedure described by Khanna and Kendall [45]. In the case of differences between the parent's and child's responses to an item, we will adhere to the guidelines provided by Grills and Ollendick [46]. This involves consolidating both reports and employing an “OR” rule to determine the presence of a symptom or diagnosis. Therefore, information gathered from the parent and the child will be merged and considered in making the final diagnostic decisions. Each disorder will receive a clinician severity rating (CSR) ranging from 0 to 8. A CSR of 4 or greater indicates the presence of a clinical diagnosis. The principal diagnosis will be the disorder(s) with the highest CSR. If a child exhibits some symptoms of a disorder but does not meet all the criteria and these symptoms affect daily functioning, the condition will be categorized as subclinical.

The absence of a diagnosis of a psychotic disorder, bipolar disorder, intellectual disability, autism spectrum disorder, and current suicidal ideation as well whether the participants have internet access to complete online sessions and proficiency in Portuguese will also be assessed during the initial interview. The child´s medication will be confirmed with the child´s pediatrician/psychiatrist or with the parents. This initial interview is expected to last approximately 90 min.

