Following Kennedy, Bilek [19], the attainment of diagnostic remission for both the principal diagnosis and all emotional disorder diagnoses at posttreatment and follow-up will be defined as the absence of the principal diagnosis and the absence of all emotional disorder diagnoses, respectively (i.e., ADIS-IV CSR < 4). A CGI-I score of 1 (*very much improved*) or 2 (*much improved*) at posttreatment or follow-up will be considered an indication of a meaningful reduction in the severity of emotional disorders and will be deemed indicative of a positive treatment response, consistent with the findings from other studies [19, 86].

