#### Attrition, nonadherence and missing data

All analyses will be performed as an intention-to-treat (ITT) analysis to ensure that the clinical efficacy of the treatment is not overestimated as an artifact of attrition (i.e., including all parents/children who completed the baseline). Missing data will be reported, and when MCAR (missing completely at random) or MAR (missing at random) occurs, multiple imputation methods will be used to estimate missing values when appropriate.

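### Diagnostic remission (ADIS CSR below 4) has no baseline condition, so children enrolled without a diagnosis count as remitted unless they worsen

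*Protocol article*

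**What the plan says.** Four statements in the protocol article bear on the point.

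- **Who is enrolled (Participants).** The population is described as "children aged 7 to 12 years with an anxiety disorder or subclinical anxiety symptoms", and the matching eligibility criterion reads "The child has a primary diagnosis of an anxiety disorder or clinically significant anxiety symptoms". A diagnosis is one route into the trial, not a requirement.
- **What counts as a diagnosis (Participant selection).** On the 0 to 8 clinician severity rating, "A CSR of 4 or greater indicates the presence of a clinical diagnosis". Of a child with some symptoms of a disorder, the text says that if the child "does not meet all the criteria and these symptoms affect daily functioning, the condition will be categorized as subclinical".
- **What counts as remission (Efficacy evaluation).** For the principal diagnosis and for all emotional disorders, remission at posttreatment and follow-up is "the absence of the principal diagnosis and the absence of all emotional disorder diagnoses, respectively (i.e., ADIS-IV CSR < 4". Nothing requires CSR 4 or more at screening.
- **Who is analysed (Attrition, nonadherence and missing data).** "All analyses will be performed as an intention-to-treat (ITT) analysis", which the same sentence explains as "including all parents/children who completed the baseline".

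The ADIS is listed under the primary outcome measures and is given at screening, posttreatment and follow-up. Categorical outcomes are compared with Pearson's chi-square test. The primary equivalence test is a TOST on the between-group difference.

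**The concern.** Remission should describe a change from having a disorder to not having it. The rule as written looks only at the end state. A child with no diagnosis at screening already satisfies it before the first session and goes on satisfying it with no benefit at all.

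Such children add the same near-certain success to both arms. The reported remission rates become too high as a description of what either programme does for children with a disorder, and the difference between the programmes becomes too small. In a trial whose stated aim is to show that two treatments are alike, dilution towards no difference is the direction to guard against, even for an outcome that does not carry the formal equivalence test.

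**Working it through.** **The plan's own figure.** The sample size uses a margin of d = 0.50, alpha 0.05, 80% power and equal allocation. With a true difference of zero, the normal approximation for TOST gives

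n per group = 2 × ((z₀.₉₅ + z₀.₉₀) / 0.50)² = 68.5, rounded up to 69, total 138.

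The stated figure reproduces. It rests on a standardized mean difference, so the definition of remission does not enter it.

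**Is a subclinical child below CSR 4?** The protocol does not give a CSR for the subclinical category. It does say that 4 or more indicates a diagnosis and that a subclinical child fails the criteria for one. Below 4 is therefore an inference, but the one that fits both sentences.

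**Dilution.** Let s be the subclinical share, equal in expectation in the two arms, and p the remission rate among children diagnosed at screening. Let w be the share of subclinical children who reach CSR 4 or more by the assessment.

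Scored remission = s(1 − w) + (1 − s)p

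If w is the same in both arms, its term cancels and the scored difference is (1 − s)(p₁ − p₂). If w differs between arms, the difference gains a term s(w₂ − w₁), so (1 − s) is approximate. The tables set w = 0.

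Neither s nor p is in the document. Assuming p = 60% vs 45%:

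| s | Arm 1 scored | Arm 2 scored | Difference |
|---|---|---|---|
| 0% | 60% | 45% | 15.0 points |
| 10% | 64% | 50.5% | 13.5 |
| 20% | 68% | 56% | 12.0 |
| 30% | 72% | 61.5% | 10.5 |
| 40% | 76% | 67% | 9.0 |

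**Effect on the chi-square comparison.** This uses a second illustration with a larger assumed contrast, 60% vs 40% among diagnosed children, 69 per arm and two-sided 0.05. The last column restricts to children diagnosed at screening, about 69 × (1 − s) per arm, where the 20-point difference is intact.

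| s | Scored rates, all children | Power, all children | Power, diagnosed only |
|---|---|---|---|
| 0% | 60% vs 40% | 65.5% | 65.5% |
| 10% | 64% vs 46% | 56.7% | 60.8% |
| 20% | 68% vs 52% | 48.3% | 55.7% |
| 30% | 72% vs 58% | 40.6% | 50.2% |
| 40% | 76% vs 64% | 33.5% | 44.3% |

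At each non-zero s shown, the restricted comparison has more power although it uses fewer children. The subclinical children bring noise to this outcome, not information.

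**The case against.** The strongest reply is about wording. The text speaks of attaining remission of a principal diagnosis, which can be read as presupposing that there was one. The intention-to-treat sentence is aimed at attrition and need not mean that children without the disorder are scored as remitted. The definition is also taken from a cited pilot trial, which may carry a baseline condition that cannot be checked here, and a condensed article may leave a denominator to the analysis plan.

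Part of this stands: the intended rule may well be the sensible one. But Participant selection defines the principal diagnosis as the disorder or disorders with the highest CSR and states no floor of 4. The second outcome, absence of all emotional disorder diagnoses, has no word that implies a diagnosis at the start. The article does not merely leave the denominator open: it fixes a definition and an analysis set which, applied together, score an unchanged subclinical child as a success.

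The second reply is about reach, and it stands in full. A reader might infer that diluted remission would produce a false finding of equivalence. The documents do not support that. The only margin is d = 0.50, for a standardized mean difference; no margin is given for proportions, and categorical outcomes go to a chi-square test of difference. Remission is derived from a primary instrument but is not named as the basis of the equivalence decision. What remains is that a non-significant chi-square could be misread as similarity.

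**Conclusion.** The point holds, for the ADIS remission outcomes only. As written, a child with no diagnosis at screening counts as remitted unless he or she worsens to CSR 4 or more. Rates are inflated in both arms and the difference shrinks by about the factor (1 − s): from 15 points to between 13.5 and 9.0 for s between 10% and 40%. The direction holds for any s above zero, provided worsening among subclinical children is similar in the two arms. The size rests on assumed values for s and for the remission rates, and at a 10% share the loss is only 1.5 points.

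A reader might go further and say that these children are remitted whatever the treatment does. That is too strong. A child who worsens to CSR 4 or more is not remitted, and a child with subclinical anxiety but another emotional disorder at CSR 4 or more does not meet the all-disorders definition at baseline. The accurate statement is that lack of benefit is scored as remission.

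The TOST on continuous scores and the sample size of 138 are untouched. This is a correction to make before analysis, not a threat to the main conclusion.

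**What to change.** State the denominators alongside the remission definition:

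- Remission of the principal diagnosis: randomised children whose principal diagnosis had CSR ≥ 4 at screening.
- Remission of all emotional disorders: randomised children with at least one emotional disorder at CSR ≥ 4 at screening.

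Compare children in the arm to which they were randomised, and report both denominators by arm, so that the subclinical share is visible. Keep subclinical children in the intention-to-treat analyses of the continuous outcomes. Because the ADIS is given before randomisation, the restriction uses baseline information only and keeps the comparison randomised.

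The cost is a sentence or two of text and no new data. The downside is a smaller denominator for remission; under the 60% vs 40% illustration, that loses less power than leaving the subclinical children in.

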#### Planned and post hoc examination of potential confounds and moderator effects

##### Covariates

Variables that are expected to correlate with but not predict outcomes differentially will be included in the baseline model to account for their effect. The targeted covariates include sociodemographic and clinical variables, such as the children’s age and sex, number of comorbid disorders, use of psychopharmacological medication, and previous psychological treatment.

##### Planned moderation analysis

Some variables will be analyzed as moderators of the efficacy of the Emotion Detectives In–Out in the primary and secondary outcomes, including the parents’ and children’s motivation to participate in the intervention, the frequency of homework assignments, both parents’ and children’s involvement in therapy, parents’ perceived barriers to the intervention, and both parents' and children's self-efficacy and enjoyment in using the internet and technology.

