#### Randomization

##### Sequence generation

After the children and parents fill out the baseline (T0) assessment measures, they will be randomly assigned at each recruitment location by a researcher not collaborating in the study and through an automated, web-based randomization program to one of two conditions: the experimental condition (Emotion Detectives In–Out) and the active control condition (Coping Cat). A permuted block randomization procedure will be employed in each location to obtain groups with an equivalent number of participants. The block size will depend on the number of eligible children in each location, but it is expected to be between 10 and 12 so that 5 to 6 participants can be assigned to each condition.

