11	Videoconference session: Questions, feedback about the child's progress, and discussion of difficulties	OTG
12	Individual exposure	F2F
13	Videoconference session: Questions, feedback about the child's progress, and discussion of difficulties	OTG
14	Individual exposure	F2F
15	Conclusion, relapse prevention, and celebration	F2F

*F2F* Face-to-face session, *OSG* Online self-guided session, *OTG* Online therapist guided session

Parents will be asked to participate in the first and last face-to-face sessions and in five online therapist-guided sessions through videoconference and to complete 10 online self-guided sessions (see Table 2). After the parents and children complete their registration, they can access the online sessions through the program's website (https://detetivesdasemocoes.pt). The online self-guided sessions include psychoeducational videos, brief exercises, and games (e.g., matching activities, problem-solving exercises). All exercises are audio-described. Homework assignments should be completed weekly on the online platform to promote the children’s interaction with the platform and keep them motivated to complete the online sessions.

**Table 2 Tab2:** Session-by-session description of the emotion detectives in–out psychological intervention (Parents)

Parents		
Session	**Theme**	**Format Delivery**
1	Introduction to the Emotion Detectives In–Out program	F2F
2	Psychoeducation about emotions and emotional parenting behaviors vs. opposite parenting behaviors. Criticism vs. positive reinforcement	OSG
3	The concept of somatization, body scanning and interceptive exposures. Criticism vs. empathy Videoconference session: Questions, feedback about the child's progress, and discussion of difficulties	OSG + OTG
4	Using science experiments to change our emotions and behaviors Criticism vs. positive reinforcement	OSG
5	The concept of cognitive flexibility and thinking traps. Different types of reinforcements and punishments. Inconsistency vs. consistent reinforcement and discipline. Nonjudgmental awareness	OSG
6	Detective thinking. Overcontrol/overprotection vs. healthy independence granting Videoconference session: Questions, feedback about the child's progress, discussion of difficulties	OSG + OTG
7	Problem-solving steps and problem-solving for interpersonal conflicts Promoting independence with detective thinking and problem solving	OSG

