#### Coping cat

Coping Cat is a cognitive behavioral therapy for children aged 7 to 13 years with anxiety disorders. In the first segment of the intervention, the children acquire several strategies that help them manage anxiety (i.e., recognizing anxiety through the identification of body cues; managing physiological activation through relaxation and diaphragmatic breathing; identifying and modifying negative automatic thoughts through cognitive restructuring; problem-solving; self-reward). The children integrate the strategies learned into a fear plan using the acronym FEAR (F = Feeling Frightened; E = Expecting Bad Things to Happen; A = Attitudes and Actions that Can Help; and R = Results and Rewards). Once the children develop these skills, they are better able to face anxiety-producing situations. Therefore, the intervention's second segment focuses on gradual exposure to anxiety-producing situations. In- and out-session group and individual exposure tasks are conducted with the children. The group version of the Coping Cat program consists of 16 weekly group sessions with 5 to 7 children per group and two individual sessions with the parents (see Table 3). The face-to-face sessions have an expected duration of 90 min and will be implemented by one clinical psychologist.

**Table 3 Tab3:** Session-by-session description of the group coping cat psychological intervention

Session	Theme	Participant
**1**	Introduction to the Coping Cat program	Child
**2**	Psychoeducation about emotions	Child
**3**	Recognizing somatic responses to anxiety	Child
**4**	Managing the somatic component of anxiety	Child
**5**	Recognizing and modifying negative cognitions	Child
**Parents’ sessions (during weeks 4 & 5)** Encouraging parental cooperation with the treatment program and gathering additional information about each child		Parents
**6**	Recognizing and modifying negative cognitions and problem-solving	Child
**7**	Developing realistic self-evaluations and using self-reward	Child
**8**	Fear plan review	Child
**Parents’ session (during weeks 8 & 9)** Updating information about each child, reviewing and summarizing the skills presented during the half part of the program, encouraging parental cooperation with the exposure segment of the treatment, and working with parents to design in vivo experiences tailored to each child		Parents
**9–11**	Exposure	Child
**12–15**	Exposure	Child
**16**	Conclusion	Child

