##### Parents’ and children’s involvement in therapy

The Parental Involvement in Therapy Scale (PITS; [23, 79) is composed of two sections. The first section asks the clinician to evaluate parents’ involvement in the therapy (i.e., communication with the clinician; parents’ attendance at the parents sessions; parents’ adherence to their own homework activities; and parents’ support of their children’s exposure exercises). The second section requires the clinician to assess the child's comprehension and application of the skills learned in the session (i.e., recognition and expression of emotions; somatic management skills; cognitive skills – recognizing dysfunctional thoughts and identifying alternative thoughts; and exposure and utilization of positive coping strategies) as well as the child’s adherence to the homework activities. Items are answered on a 5-point Likert scale that ranges from 0 to 4.

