### Statistical methods

#### Efficacy evaluation

The efficacy of the Emotion Detectives In–Out in comparison with the Coping Cat will be assessed by analyzing the changes in the primary and secondary outcomes. As an equivalence clinical trial, the aim is to test whether the Emotion Detectives In–Out (experimental condition) is as effective as the Coping Cat (control group). The planned analysis for each outcome is a repeated-measures linear mixed model adjusted for covariates. The primary equivalence testing will be the between-group difference TOST at postintervention and at 3 months using the Welch correction for heterogeneous variance if needed. We will also investigate the linear and nonlinear (quadratic) effects for time and condition and simple effects for parameter estimates within each condition. For categorical variables (e.g., treatment response as assessed by CGI-I), treatment conditions will be compared using Pearson’s chi-square test.

To examine for heterogeneous intervention response, we will calculate Reliable Change Indices (RCI) for all participants at postintervention and at the 3-month follow-up. The RCI will be calculated for all outcomes and correlated with demographics to examine for subgroup efficacy predictors. The cutoff for clinically significant change is generally accepted as ± 1.96 [81]. Likewise, we aim to test the longitudinal trajectory of anxious symptoms over time using Growth Mixture Modeling (GMM). Furthermore, assuming that heterogeneous trajectories of anxious symptoms are observed, we aim to test the suitability of the collected demographic variables as predictors of group membership.

For the primary equivalence, efficacy, RCI, and chi-square analyses, we will use Jamovi software and the GAMLj and TOSTER packages as needed [82]. For GMM analyses, we will use R software with the package *lccm* [83] to perform growth mixture modeling, and evaluate various model specifications of *k* classes two through six, and using both fixed and random effects. We will select the optimal number of clusters was based on four criteria: parsimony, entropy approaching 1, lowest BIC/SABIC, and minimum class size > 10% of the sample [84, 85].

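### Homework frequency and involvement in therapy arise after randomisation, so between-arm moderation estimates that condition on them can be biased; the primary equivalence test is not affected

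*Protocol article*

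**What the plan says.** The Planned moderation analysis section states: "Some variables will be analyzed as moderators of the efficacy of the Emotion Detectives In–Out in the primary and secondary outcomes". Its list puts "the frequency of homework assignments, both parents’ and children’s involvement in therapy" alongside motivation, perceived barriers, and technology self-efficacy and enjoyment, and gives all of them the same role.

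Other sections fix what these words mean:

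- **Efficacy is a between-arm contrast.** Efficacy evaluation: "The efficacy of the Emotion Detectives In–Out in comparison with the Coping Cat will be assessed by analyzing the changes".
- **Randomisation comes before therapy.** Sequence generation: "After the children and parents fill out the baseline (T0) assessment measures, they will be randomly assigned".
- **Involvement is rated from what happens in therapy.** Of the involvement scale: "The first section asks the clinician to evaluate parents’ involvement in the therapy". This part covers attendance at parent sessions, parents' homework and their support of exposure. Of the child part: "The second section requires the clinician to assess the" child's understanding and use of the skills taught, and the child's homework.
- **Parent contact differs by arm.** Coping Cat has "two individual sessions with the parents". In Emotion Detectives In–Out, parents join the first and last face-to-face sessions, five videoconferences and 10 self-guided sessions. The Objectives list greater parental involvement as an expected advantage of the new program.
- **Homework differs by arm.** In the new program: "Homework assignments should be completed weekly on the online platform". The Feasibility section takes its completion from platform data. The Acceptability section gives Coping Cat parents only two questions, both about supporting homework.

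**The concern.** A moderator of a randomised effect describes who benefits more from one arm than from the other. For the comparison at each level of the moderator to stay randomised, allocation must not be able to influence the moderator. Homework frequency and involvement do not exist at allocation. They are produced during treatment, and the child part of the involvement rating is close to a treatment result.

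Suppose the new program raises involvement, and families with a better outlook also engage more. Then, at the same involvement score, an Emotion Detectives family and a Coping Cat family are not alike in prognosis: the former reached that score with help from the program's design. With higher involvement in the new arm, the distortion makes the new program look worse at a given level of involvement. Separately, if the rating reflects prognosis more closely in one arm than in the other, a moderation effect can appear where none exists.

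At stake is a secondary result, but one that could be read for or against the equivalence conclusion. Analysing by intention to treat keeps every family in the model; it does not remove this bias.

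**Working it through.** **1. The plan's own figure.** The article gives no figure for the moderation analysis, so only the sample size can be reproduced. TOST, true difference 0, margin d = 0.50, alpha 0.05, power 80%:

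n per arm = 2 × ((1.645 + 1.282) / 0.50)² = 68.5, rounded up to 69, total 138. With 15% attrition, 138 / 0.85 = 162.4, so 163, in line with the article's approximate 165. The sample size is not in dispute; 69 per arm is used below.

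**2. Model.** True arm effect and true moderation are both zero. An unmeasured prognostic factor U (SD 1) drives outcome Y (correlation c; higher is better) and the post-randomisation variable M (correlation b0 in Coping Cat, b1 in Emotion Detectives). The arm shifts M by s SD. Y is regressed on arm, M centred at its overall mean, and arm × M, with two-sided tests at 0.05. On a symptom scale the signs reverse, but the distortion still goes against the new program.

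**3. Expected coefficients.** The within-arm slope of Y on M is b × c. With equal arms:

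- arm coefficient at average M = −s × c × (b0 + b1) / 2
- interaction = c × (b1 − b0)

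For example, s = 1 and b0 = b1 = c = 0.5 give −1 × 0.5 × 0.5 = −0.25; b0 = 0.2, b1 = 0.6, c = 0.5 give an interaction of 0.5 × 0.4 = 0.20.

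**4. Simulation.** All of s, b0, b1 and c are assumptions. 4,000 trials per row; 6,000 in the two rows marked *.

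| s | b0 | b1 | c | Arm coefficient: formula / simulated | False arm effect | Interaction: formula / simulated | False interaction |
|---|---|---|---|---|---|---|---|
| 0 | 0.5 | 0.5 | 0.5 | 0 / −0.002 | 4.7% | 0 / 0.000 | 5.0% |
| 1 | 0 | 0 | 0.5 | 0 / −0.002 | 4.8% | 0 / 0.003 | 5.6% |
| 0.5* | 0.3 | 0.3 | 0.3 | −0.045 / −0.045 | 5.8% | 0 / −0.004 | 5.2% |
| 0.5 | 0.5 | 0.5 | 0.5 | −0.125 / −0.126 | 10.5% | 0 / 0.000 | 5.0% |
| 1 | 0.3 | 0.3 | 0.5 | −0.15 / −0.151 | 11.9% | 0 / 0.001 | 5.4% |
| 1 | 0.5 | 0.5 | 0.5 | −0.25 / −0.250 | 26.4% | 0 / 0.000 | 5.0% |
| 1 | 0.7 | 0.7 | 0.7 | −0.49 / −0.489 | 83.4% | 0 / −0.002 | 4.9% |
| 0* | 0.3 | 0.6 | 0.5 | 0 / 0.000 | 5.1% | 0.15 / 0.146 | 13.6% |
| 0 | 0.2 | 0.6 | 0.5 | 0 / −0.002 | 4.8% | 0.20 / 0.199 | 21.5% |
| 1 | 0.2 | 0.7 | 0.7 | −0.315 / −0.316 | 40.9% | 0.35 / 0.347 | 56.6% |

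**5. Reading.** A false arm effect needs both an arm shift and a shared cause with outcome. A false interaction needs M to track prognosis differently in the two arms, and can occur with no shift. The first row is the baseline-moderator case, where error is nominal. The unadjusted randomised difference stayed at zero throughout, apart from simulation noise.

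**The case against.** **It is a supplementary analysis.** This stands. Equivalence rests on the between-group TOST at postintervention and 3 months, and the covariates named in the Covariates section are sociodemographic and clinical background variables. A reader might infer that the randomised comparison or the equivalence conclusion is compromised; the article does not support that.

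**No moderation model is given, and a within-program analysis may be meant.** The Objectives aim to find predictors of adherence to the new program and of treatment outcomes, and an analysis plan not shown may set out the model. That reading is possible, but the section is about moderators of efficacy, and efficacy is defined against Coping Cat. If within-program prediction is meant, the wording still needs changing.

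**A moderation analysis tests the interaction, not the arm coefficient.** Largely right. The larger error rates belong to the arm difference at average involvement, which the article does not say will be reported. Centring M within each arm removes that bias and returns the rate to about 5–6% at moderate correlations. It does not help the interaction, which stays distorted when the tracking is unequal.

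**The arm shift is not established.** Session counts do not settle a 0–4 rating, since attendance can be scored against each program's own schedule. The Objectives' expectation of greater parental involvement makes a shift plausible; its size is unknown. A reader might want one headline error rate, but none is defensible: with a shift of 0.8, an outcome loading of 0.6 and involvement loadings of 0.6 in both arms or 0.9 and 0.3, the false arm effect is 50–63% if residual SDs are 0.8 (outcome) and 0.6 (involvement), but only 15–18% if both are 1.

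**Conclusion.** The concern holds for the planned moderation analysis. Two of the listed variables are generated after randomisation, one of them partly measures response, and the arms differ by design in what feeds both. Treating them as moderators of a between-arm effect can therefore give biased estimates.

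The size cannot be read from the article. In the equal-correlation scenarios with a shift, the bias in the arm difference at average involvement runs from about 0.13 SD (a quarter of the 0.50 margin) to 0.49 SD (nearly all of it). With the weakest inputs it is 0.045 SD and hardly matters, and with no shift or no shared cause it vanishes. The interaction test keeps its error rate if involvement tracks prognosis equally in both arms; under unequal tracking it rises to about 14–22%, and to 57% in the strongest scenario. The change should be made, but it concerns a secondary analysis only.

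**What to change.** 1. Restrict arm-by-variable moderation models to variables measured before randomisation. Motivation, expected barriers, and technology self-efficacy and enjoyment qualify through their T0 values where these are collected. The visible text does not state their timing and the schedule figure is not shown, so the section should say that T0 values are used.
2. Move homework frequency and parents' and children's involvement to within-arm process (dose-response) analyses, labelled as non-randomised associations. If a causal question is intended, pre-specify a mediation analysis and state its assumption of no unmeasured common cause of the process variable and the outcome.
3. If homework is described side by side across arms, state how it is counted in each, because the sources described differ.

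The cost is a change of analysis wording; data collection stays as it is. The downside is that these two variables no longer support claims about for whom the new program works better than Coping Cat.
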